**Figure 1 F1:**
[figure not shown]
**Effect of Provider Interventions on the Treatment Received by Patients**.

### Outcomes

#### Primary outcome

The primary outcome is the proportion of patients attending facilities that report a fever or suspected malaria and receive treatment according to malaria guidelines. The corresponding measure of cost-effectiveness is the cost per febrile patient that receives treatment according to the malaria guidelines.

Treatment according to the malaria guidelines is a composite endpoint requiring that:

• Febrile patients should be tested for malaria, using either microscopy or an RDT

• The patient should receive an ACT if he/she has a positive malaria test result

• The patient should not receive an antimalarial if he/she has a negative malaria test result

The outcome measure is summarized in Figure 2.

**Figure 2 F2:**
[figure not shown]
**Primary outcome measure**.

#### Secondary outcomes

Secondary outcomes include:

• Proportion of febrile patients that are tested for malaria

• Proportion of febrile patients receiving an antimalarial that receive an ACT

• Proportion of febrile patients receiving an ACT that receive the correct dose for their age

• Proportion of febrile patients receiving an ACT that accurately report how to take the medicine

• Proportion of febrile patients that report they are satisfied with the care received

• Proportion of HWs that report they were satisfied with the training received

• Proportion of HWs that know ACT should be given if the malaria test is positive and that an antimalarial should not be given if the malaria test is negative

• Proportion of HWs that report febrile patients should be tested for malaria

• Proportion of HWs that know how to identify positive, negative and invalid malaria RDT results

• Proportion of HWs that know the correct dose of the first-line ACT in an adult and in a child aged 2 years

• Total cost of the provider interventions and the cost per HW attending the BT and ET

Secondary outcomes related to patients will also be reported in terms of their urban/rural residence and socioeconomic status.

### Evaluation design

The evaluation of the intervention will use data collected in a patient exit survey, a register of malaria tests conducted by the provider during patient consultations, a provider survey, documentation of the intervention process, costing of the intervention activities and lastly, independent testing of malaria by the study team (see 'quality assurance'). The patient exit survey will be administered before the provider survey to ensure that the treatment received by patients is not influenced by the content of the provider questionnaire. Each of these is described below.

#### Patient exit survey

The primary outcome will be measured through an interviewer-administered patient exit survey. Data collection will commence three months after the intervention has been implemented. The three-month lag in the data collection is to ensure that the effect measure reflects treatment practices in the medium-term. In the short-term it is recognised that it is possible that the effect is overstated because health workers may change practices initially but revert to past behaviours over time, or that the effect is understated because it takes time for the training to have an effect as some health workers are hesitant and want to learn from the experience of the early-adopters. The survey data collection will take up to two months and will be organized such that the data will show the effect of the intervention over this time period by establishing a maximum number of patients that can be surveyed each week.

The research team will recruit field workers and provide training over a week on all aspects of data collection related to the patient exit survey. The training will include a practical assessment of their ability to provide information to respondents about the survey, obtain consent and administer the questionnaire. The research team will supervise the field workers and will accompany the field worker at the start of data collection to obtain consent from the head of the facility and ensure the fieldworker adheres to the standard operating procedures. Supervisory visits to monitor the performance of the field workers will take place at least once each week during the data collection period.

The patient exit questionnaire is designed to collect information about the patient's experience of seeking treatment and has been piloted a selected facilities in the study site. The questionnaire contains the following ten modules:

A. Background Information, Consent and Screening Questions

B. Details of the Respondent and/or Patient

C. Reasons for attendance

D. Consultation and diagnosis

E. Treatment prescribed and received

F. Patient satisfaction and knowledge of malaria

G. Costs of seeking treatment

H. Household characteristics

I. Malaria test completed by the study team (in sub-sample of patients)

J. Malaria test completed by health workers (from register of malaria tests at facility)

#### Register of malaria tests conducted

The patient exit questionnaire will be supplemented by a register of malaria tests at each participating health facility because patients may not always know if they were tested for malaria and the result of the malaria test. With consent from the head of the facility, health workers responsible for conducting malaria tests will be asked to keep a register of all malaria tests undertaken. The following data will be collected: details of the patient, availability of microscopy and RDT, method of test conducted, test result and the provider that conducted the test. At each facility the field workers will collect the register of malaria tests at least once each week and will use the patient's name, gender, age, date of visit to identify the patients that completed the survey and record the details in Section J of the questionnaire.

#### Provider Survey

The research team will administer a provider survey to all providers responsible for the diagnosis and treatment of suspected cases of malaria. Providers are eligible to participate if their responsibilities include any of the following activities: taking patient signs and symptoms, undertaking diagnostic tests, prescribing or dispensing medication. Written informed consent will be obtained before commencing the survey.

The provider survey has been designed to collect data on the providers' characteristics, knowledge and preferences for diagnosing and treating malaria and details of the resources available at the health facility. The survey will be piloted with providers at facilities that are not participating in the study. The questionnaire contains the following modules (of which A-B are completed by all providers and C-G are completed once for each facility):

A. Background information, consent and screening questions

B. Health worker characteristics and treatment practices

C. Details of the health facility

D. Management and procurement of drugs

E. Availability of RDTs

F. Availability of Antimalarials

G. List of all health workers that are involved in diagnosis or treatment

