#### Basic Provider Training (BT)

Facilities randomised to the basic intervention will be supplied RDTs and receive basic provider training on malaria diagnosis and treatment. This training is intended to mimic the style of workshop that is routinely implemented as in-service health worker training. The training will be conducted over one day and contain three training modules: 1) Malaria Diagnosis; 2) Rapid Diagnostic Testing; 3) Malaria Treatment. Together these three training modules will provide health workers with the knowledge and skills on why malaria testing is recommended, how to use an RDT, the treatment algorithm and details contained in the malaria guidelines. The malaria guidelines state how confirmed cases of uncomplicated malaria should be treated, including advice on dosing and treatment regimens for different types of ACT. The training also provides advice on other causes of febrile illness which should be investigated if the malaria test is negative. The module on RDTs includes a practical session in which all health workers will get hands-on experience of the steps involved in using an RDT.

The training will be conducted in conference halls of health districts located in both study sites. The following types of providers will be invited to the training: medical doctors, nurses, laboratory technicians and pharmacy attendants. Each facility will be invited to select 3 providers to attend the training. The training will be conducted jointly by medical doctors, representatives of the national malaria control programme and the research team. The trainers will receive extensive briefing by the research team and given a trainer's manual which provides detail of the material for each module and how it should be delivered. The training manual also includes standardized power-point presentations. In addition, the trainers will be trained in presentation and communications skills.

Each basic training workshop will train 25-30 providers. The training primarily takes a didactic seminar style in which the trainer delivers the training material, though there is scope for questions and discussion. A participant's training manual will be given to providers that attend the training course and includes all essential reference material including the malaria treatment guidelines. Participants will also be provided with job aids for RDTs and a treatment algorithm to be placed on their tables while in their health facilities.

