### Randomisation

A total of 47 facilities, 23 in Bamenda and 24 in Yaoundé, will be randomised within stratum to receive current practice, the basic intervention (RDTs and basic training) or the enhanced intervention (RDTs with enhanced training). With cluster randomised trials there is an increased chance that the study arms are unbalanced with respect to known and unknown potential confounders, and therefore undermines the credibility of the trial results. Stratified randomisation will reduce the likely imbalance in factors known to be correlated with the study outcome and the study site. However, the current availability of microscopy and the type of facility (which will also capture variation in health worker and patient characteristics) were assumed to be important correlates and therefore a process of constrained, or restricted, randomisation [34,35] will also be implemented to balance these two factors across the study arms using data collected in the formative research.

Using restricted randomisation schemes increases the risk of producing a design which is biased and not valid. Moulton [35] describes a design as being biased if there is any difference across the clusters in their probability of allocation to any given treatment. A randomised design is said to be valid if every pair of clusters has the same probability of being allocated to the same treatment. If the design is not valid there is a risk that the Type I error changes from its nominal value of 0.05. We will assess the validity of the restricted randomisation by producing a matrix where the rows and columns represent the clusters and the elements of the matrix are the proportion of times each pair of clusters is allocated to the same study arm i.e. the probability that the i^th ^cluster is being allocated to the same intervention group as the j^th ^cluster. The matrix will then be examined for under- and over-represented pairs that would highlight any potential causes for concern in the randomisation.

Randomisation of the facilities will be performed by the study statistician after informed consent has been sought from the head of the facility to avoid selection bias. Patients (or caregivers) and fieldworkers administering the patient exit survey will be blinded to group assignment. The research team involved in implementing the training interventions and supervising data collection will need to be aware of which facilities receive the different interventions.

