Secondary outcomes on treatment received by patients, and provider knowledge and practice, will be analysed using the methods described above. To examine whether secondary outcomes vary according to the urban/rural residence and socioeconomic status of the patients methods appropriate for examining an interaction between the intervention and the individual-level variable will be applied [36]. Differences in coverage estimates between the intervention arms will also be estimated by calculating the arithmetic mean of the coverage proportions in each cluster and conducting a two-way analysis of variance, allowing for stratification.

For the economic analysis, cost-effectiveness ratios will be based on the primary outcome (i.e. the cost per case of suspected malaria that received treatment as recommended in the malaria guidelines) as well as a range of secondary outcomes including changes in provider knowledge. Cost-effectiveness will be calculated for each comparison and will be expressed as incremental cost-effectiveness ratios (ICERs). One-way and multi-way sensitivity analysis will be undertaken to examine the effects of varying uncertain variables on study findings. Costs and effects will be presented in both discounted and undiscounted form.

All data will be double entered using Microsoft Access 2007 (Microsoft Inc., Redmond, Washington) and analysed using STATA version 11.0 (STATA Corporation, College Station, Texas). A full analysis plan will be reviewed and agreed before the data are analysed.

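### The provider-knowledge survey is assigned to the research team that helps train the intervention arms, with no stated separation or masking, so knowledge comparisons with control may favour training

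*Protocol article*

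**What the plan says.** All references are to the protocol article.

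- **Who collects the data.** Provider Survey: "The research team will administer a provider survey to all providers responsible for the diagnosis and treatment of suspected cases of malaria". On content: "The provider survey has been designed to collect data on the providers' characteristics, knowledge and preferences for diagnosing and treating malaria".
- **Who trains.** Basic Provider Training (BT): "The training will be conducted jointly by medical doctors, representatives of the national malaria control programme and the research team". The enhanced course opens with the same one-day basic modules; its own section does not name the trainers.
- **Who supplies RDTs.** Under Supply of RDTs, members of the research team deliver the tests monthly. Only the two intervention arms receive them.
- **Who knows the allocation.** Randomisation: "The research team involved in implementing the training interventions and supervising data collection will need to be aware of which facilities receive the different interventions".
- **Who is blinded.** Randomisation: "Patients (or caregivers) and fieldworkers administering the patient exit survey will be blinded to group assignment". No statement of this kind is made for the provider survey.
- **What depends on it.** Secondary outcomes lists four knowledge items: when to treat (for example, "Proportion of HWs that know ACT should be given if the malaria test is positive"), whom to test, how to read an RDT, and the first-line ACT dose. Data analysis: "Secondary outcomes on treatment received by patients, and provider knowledge and practice, will be analysed using the methods described above". The Abstract and Data analysis also base cost-effectiveness ratios on changes in provider knowledge.

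**The concern.** The protocol separates outcome assessment from the intervention for the exit survey: recruited field workers, blinded to arm, interview the patients. For the provider survey it does the reverse and names the group that takes part in training and RDT supply. A provider in a trained facility may be questioned by someone from the team that taught or supplied that facility. A control provider has had neither contact as part of the study.

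Three mechanisms could act in one direction only: prompting, generous scoring of a borderline answer, and a respondent's wish to give a trainer the expected answer. Each would raise apparent knowledge in the trained arms. The confidence interval would not show it, because a shift shared by trained facilities looks the same as a training effect. At stake are the basic-versus-control and enhanced-versus-control knowledge comparisons and the secondary cost-effectiveness ratios built on them.

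**Working it through.** **1. Is there a stated safeguard?**

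- Evaluation design puts the exit survey before the provider survey. That protects the exit survey from the provider questionnaire; it does not mask the provider survey.
- Documentation of the Intervention Process describes a pre- and post-training test. Only training participants sit it, so it gives no comparison with control.
- Independent verification of malaria tests adds outside checks on recorded test results. Nothing similar is stated for knowledge answers.
- No passage keeps trainers or RDT deliverers from administering the provider survey.

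**2. The plan's own precision.** Inputs from Sample size, Provider survey: p = 0.90, ICC = 0.1, m = 3 to 4 providers per facility, 9 control facilities and 19 per intervention arm. Half-width for one arm of k facilities:

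1.96 × √[p(1−p) × (1+(m−1)×0.1) / (k×m)]

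| m | control, k = 9 | intervention, k = 19 |
|---|---|---|
| 3 | 12.4 | 8.5 |
| 3.5 | 11.7 | 8.1 |
| 4 | 11.2 | 7.7 |

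The stated ±11.8 and ±7.7 points lie within or at the edge of these ranges, though no single m gives both. This has no bearing on the point.

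**3. Precision of an intervention-control difference**, with 90% in both arms:

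- m = 3: 0.09 × 1.2 = 0.108; 0.108/27 + 0.108/57 = 0.00589; SE 7.68 points; half-width 15.0.
- m = 3.5: 0.09 × 1.25 = 0.1125; 0.1125/31.5 + 0.1125/66.5 = 0.00526; SE 7.25 points; half-width 14.2.
- m = 4: 0.09 × 1.3 = 0.117; 0.117/36 + 0.117/76 = 0.00479; SE 6.92 points; half-width 13.6.

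**4. Upper limit on the bias.** At 90% correct, 10% of answers are wrong. Turning every one of them right moves the arm by 10 points, which is below every half-width in step 3.

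**5. Effect of an assumed shift.** Take no true difference, a 5-point upward shift in the trained arm (assumption) and m = 3.5. The shift is 5/7.25 = 0.689 SE. The two-sided false-positive risk is

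Φ(0.689 − 1.96) + Φ(−0.689 − 1.96) = 0.102 + 0.004 = 0.106,

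or about 11% instead of 5%. For m = 3 and m = 4 it is 10.0% and 11.2%. These keep the variance at 90% in both arms. With the trained arm's variance taken at 95% (0.95 × 0.05 = 0.0475), the SE at m = 3.5 is √(0.00357 + 0.0475 × 1.25/66.5) = 6.68 points and the risk is about 12%.

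**The case against.** The strongest case against has five parts.

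- **Mode of the survey.** A reader might infer that providers are interviewed. The text says only that the survey is administered, whereas the exit survey is expressly interviewer-administered. If providers fill in the form themselves, prompting largely falls away. The general consent text mentions interviewers explaining the study to all participants, which makes an interview likely but does not settle it. This limits the point to a risk.
- **Same individuals.** A reader might infer that trainers survey the people they taught. The documents do not say so. Training is shared with medical doctors and national programme representatives, trainers are briefed by the research team, and the Randomisation sentence can be read as describing a subset of that team. Each facility sends three providers to training, while all eligible providers are surveyed, so some respondents may never have met a trainer. This stands. But the assignment is made to the team as a whole, and no separation is stated.
- **Condensed article.** Response format and scoring key may sit in the questionnaire or operating procedures, and their absence here is no fault. The point rests on what the article does state: who administers the survey, and whose blinding is claimed.
- **Room for discretion.** Reading an RDT result or naming a dose has a fixed right answer, which leaves less scope for lenient scoring. This stands and argues for a modest bias.
- **Masking is limited.** Field workers collect test registers that show RDT availability and test method, and module E of the provider survey asks about RDT availability. They could infer RDT versus control. This stands, so a change of assessor alone is not enough.

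**Conclusion.** The point holds as a risk to secondary outcomes. The article gives the provider survey to a team with a part in training and RDT supply, some of whom must know the allocation, and it states neither separation of trainers from assessors nor masking. The four knowledge outcomes and the ratios based on them may favour training over control.

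Three stronger readings are not supported. First, the knowledge results are not shown to be biased: no passage demonstrates a shift or gives its size. Second, the bias cannot be as large as the half-width on the plan's own inputs: at 90% correct it is capped at 10 points, against 13.6 to 15.0. A larger shift would require true knowledge below 90%. Third, the primary outcome and its cost-effectiveness ratio are not touched, since they come from the exit survey with blinded field workers. The enhanced-versus-basic comparison is less exposed because both arms share the link with the team.

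The rise from 5% to about 11% rests on an assumed 5-point differential shift, no true difference, 3.5 providers per facility and a normal approximation. It illustrates the effect and does not estimate it.

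**What to change.** Amend Provider Survey so that, once the exit survey has closed at a facility, the provider survey there is administered by existing team members or field workers who took no part in training or RDT delivery. Record knowledge answers as fixed options or verbatim, and score them against a key set in advance by someone masked to facility and arm. State as a limitation that assessors may still infer the arm from RDT availability; masked scoring is therefore the main protection.

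The cost is a sentence or two in the protocol, some briefing of the assessors (field workers may need help with technical items) and the masked scoring step. Drawing on existing staff should avoid new posts. Trial status says recruitment for the exit survey is under way. If provider surveys have already begun, masked rescoring of the recorded answers and the stated limitation remain possible.

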#### Documentation of the Intervention Process

The implementation of the malaria training workshops delivered to health workers will be documented. Details of all participants attending the training course will be recorded. Participants will undertake a pre- and post-training test to determine the impact of the training on their knowledge of malaria diagnosis and treatment. All participants will be invited to complete the training evaluation, which assesses the content and delivery of the training course. In addition, the trainers will complete a form to record any challenges faced in running the training workshop. Finally, the process of distributing the RDTs to health facilities will be monitored and any problems with the procedures for replenishing RDT stocks will be documented.

#### Costing

Direct and indirect costs of each phase of the interventions (i.e. development, implementation, upkeep) will be assessed from both a provider and societal perspective using standard economic evaluation methodologies [32]. Cost data will primarily be estimated from health facility records, project financial accounts and from the provider and patient exit surveys. Any health care savings will also be included and subtracted from costs.

